### Endpoints

The efficacy and safety endpoints are presented in Table 3. In brief, the primary efficacy endpoint is the total time needed to ablate and eliminate all targeted LAVAs. The secondary efficacy endpoints include other procedural metrics (including postprocedural inducibility, total procedural duration, and fluid balance) and time-dependent outcome metrics such as total mortality, hospital admissions for cardiovascular indication, and recurrences of VT/ventricular fibrillation. Safety endpoints include a range of possible periprocedural complications, with particular attention paid to issues that may be more relevant to PFA; this includes any coronary events (including coronary vasospasm), acute kidney injury, and changes in LVEF and/or evidence of new wall motion abnormalities.

**Table 3 tbl3:** Efficacy and safety endpoints

Primary efficacy endpoint	Objective/rationale
Time needed to eliminate LAVAs	This is the primary procedural efficacy metric highlighting a key potential advantage of PFA over RFA technology.
Acute secondary efficacy endpoints	Objective/rationale
Total procedural duration	These are additional procedural efficacy metrics expected to mirror the primary efficacy endpoint.
Total fluid administered by the ablation catheter	
Total fluid administered during the procedure	
Fluid balance at the end of the procedure	
Ongoing presence of LAVAs at the end of the procedure	A different efficacy metric. LAVA elimination may not always be possible with RFA and is likely always feasible with PFA, although the durability of this elimination remains to be determined.
VT noninducibility at the end of the procedure	A standard acute endpoint metric, although its utility has lately been challenged^45^
Time-dependent secondary efficacy endpoints (assessed 6 mo postoperatively)	Objective/rationale
Recurrences of sustained VT leading to appropriate ICD interventions (ATP or shock) or any symptomatic sustained VT	Standard clinical follow-up endpoints. The ASCEND-VT trial is not powered to show significant differences in these outcomes. However, if major differences are ultimately observed in these metrics, future studies will have to elucidate whether the procedural workflow of PFA needs to be adjusted.
Any documented sustained VT below the detection rate of the ICD	
All-cause mortality	
VT burden (number of appropriate ICD therapies in the 6 mo before ablation vs 6 mo after the ablation)	
Hospital admissions for cardiovascular causes	

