Primary safety endpoints (assessed ≤7 d postoperatively)	Objective/rationale
Cardiac perforation	Benchmark safety data from the ThermoCool VT trial^10^ were based on similar endpoints.
Pericardial effusion with hemodynamic compromise or needing intervention	
New complete heart block	
Coronary spasm	
Acute MI	
New acute severe mitral regurgitation or aortic regurgitation	
Deep venous thrombosis	
Vascular injury requiring surgical or percutaneous intervention	
Pulmonary embolism	
Stroke	
Acute kidney injury (>0.5 mg/dL increase in creatinine from baseline within 24 h after the procedure)	
Death	
Secondary safety endpoints (assessed during follow-up)	Objective/rationale
Device- or procedure-related SAEs (the proportion of subjects in each treatment arm with at least 1 device- or procedure-related SAE)	Summary metric of SAE frequency
Acute kidney injury	Metrics of particular relevance to the PFA technology
Coronary vasospasm at any point during follow-up	
Changes in LVEF and/or new wall motion abnormalities at follow-up TTE (180 d)	

ATP = antitachycardia pacing; ICD = implantable cardioverter-defibrillator; MI = myocardial infarction; LAVA = late abnormal ventricular activity; LVEF = left ventricular ejection fraction; PFA = pulsed field ablation; RFA = radiofrequency ablation; SAE = serious adverse event; TTE = transthoracic echocardiogram; VT = ventricular tachycardia.

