The ASCEND-VT study will also look at hard clinical outcomes such as VT recurrences and all-cause mortality, although the power to detect any signal in this realm may be limited. Indeed, establishing overall clinical noninferiority of 1 ablation technology over another, for example, proving that the use of PFA results in lower VT recurrence or lower mortality than RFA, will necessitate a large-scale multicenter trial with an extended follow-up time. However, ASCEND-VT will provide important early information to design a large head-to-head comparative trial.

The ASCEND-VT study is also intended to systemically assess the safety of PFA in ICM VT ablations. Although the rate of vascular or major mechanical cardiac adverse events (eg, pericardial effusion and tamponade) is expected to be comparable between the 2 study arms, certain potential complications are relatively specific to PFA and will need to be separately assessed. First, early PFA literature (particularly in the context of atrial ablation) has shown that transient hemolysis is a relatively frequent consequence of PFA ablation, although the incidence of resulting end-organ damage is very low.^28^^,^^41^^,^^42^ For this reason, the ASCEND-VT trial will specifically track the rate of acute kidney injury after the procedure. Second, PFA in the atrium may result in vasospasm when applied in the vicinity of coronary arteries^26^^,^^43^; although patients in ASCEND-VT will only be subjected to ventricular endocardial PFA applications (ie, not near the epicardial coronary vessels), the possibility of vasospasm with or without substantial myocardial injury will be closely tracked. However, the potential for vasospasm is not unique to PFA alone, having previously been demonstrated with RFA, and will be evaluated in both arms. Third, even in the absence of new coronary injury, there is a theoretical concern that the uniform and large PFA lesions may have an effect on myocardial contractility, especially if applied outside of noncontractile scar^44^; therefore, the ASCEND-VT trial will pay particular attention to any perturbations in LVEF and/or evidence of new wall motion abnormalities after ablation.

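### The only SAE summary in Table 3 counts just the SAEs judged related to device or procedure, so it does not measure SAE frequency and can reflect attribution

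*Protocol article*

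**What the plan says.** In the Endpoints section, Table 3 has a block headed "Secondary safety endpoints (assessed during follow-up"). Its first row is "Device- or procedure-related SAEs (the proportion of subjects in each treatment arm with at least 1 device- or procedure-related SAE"), and the rationale beside it reads "Summary metric of SAE frequency". No row counts SAEs regardless of cause.

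The other safety and clinical rows carry no relatedness condition. The block "Primary safety endpoints (assessed ≤7 d postoperatively") names 12 events, death among them. The remaining secondary safety rows are acute kidney injury, "Coronary vasospasm at any point during follow-up", and change in LVEF or new wall motion abnormality at 180 days. The 6-month secondary efficacy rows include "All-cause mortality" and "Hospital admissions for cardiovascular causes", along with VT recurrence.

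The Discussion says that "certain potential complications are relatively specific to PFA and will need to be separately assessed", and adds that vasospasm will be looked at in both arms. The article does not use the term open-label. However, the arms use different ablation catheters (Substrate ablation) and different mapping systems (Discussion, limitations), so the operator knows the allocation.

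**The concern.** The row and its rationale do not agree. A count of related SAEs is a device-safety measure. A summary of SAE frequency would count all SAEs. Someone who takes the rationale at face value would read the related-only proportion as the SAE rate of each arm.

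The difference matters because relatedness is a judgement that may depend on the arm. One arm uses an investigational catheter with a list of anticipated complications, and the other uses commercially available catheters. The same event may be ascribed to the device in one arm and to the underlying disease in the other. The tilt could go either way: expectation may raise attribution after PFA, and confidence in the device may lower it. Randomisation makes the judgement unnecessary for a comparison between arms, since unrelated events should balance apart from chance.

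At stake is the SAE line of a pilot whose Discussion intends to speak of comparable safety profiles and to inform a larger trial.

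**Working it through.** **Step 1. What the other endpoints already cover without a relatedness judgement (Table 3).**

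- Up to 7 days: the 12 named events.
- During follow-up: acute kidney injury, coronary vasospasm, LVEF and wall motion at 180 days.
- At 6 months: death from any cause, cardiovascular admissions, VT recurrence.

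**Step 2. What is left.** An SAE goes uncounted if it is judged unrelated and is not on those lists. Two groups remain:

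- Serious events during the index stay outside the 12, such as acute heart failure, an anaesthetic or respiratory complication, or bleeding that needs no surgical or percutaneous intervention. They would not obviously count as an admission, because the patient is already in hospital.
- Nonfatal, non-cardiovascular SAEs later in follow-up.

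The first group bears on the trial's own rationale. The Introduction and Discussion argue for PFA partly through less irrigation fluid and shorter anaesthesia. Fluid overload and anaesthetic complications are not among the 12 events and can readily be ascribed to underlying disease. The related-only count could therefore hide a PFA advantage as easily as a PFA harm.

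**Step 3. How far attribution alone can move the metric.** The plan gives no SAE rate, so there is no figure of its own to reproduce on this point. The arm size comes from the plan: 36/0.9 = 40 patients, randomised 1:1, hence about 20 per arm. Everything else is assumed.

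Let p be the true proportion of patients with an SAE, equal in both arms, and let a1 and a2 be the probabilities that the SAE is called related. For simplicity, each affected patient is treated as having one SAE. The counts are then X ~ Bin(20, p·a1) and Y ~ Bin(20, p·a2). For p = 0.30, a1 = 0.70 and a2 = 0.30, the expected proportions are 0.30 × 0.70 = 21% and 0.30 × 0.30 = 9%. Summing the joint binomial probabilities gives:

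| p | a1 / a2 | Expected related SAE | P(X > Y) | P(X < Y) |
|---|---|---|---|---|
| 0.30 | 0.50 / 0.50 | 15% / 15% | 0.41 | 0.41 |
| 0.30 | 0.60 / 0.40 | 18% / 12% | 0.62 | 0.22 |
| 0.20 | 0.70 / 0.30 | 14% / 6% | 0.72 | 0.13 |
| 0.30 | 0.70 / 0.30 | 21% / 9% | 0.81 | 0.09 |
| 0.40 | 0.70 / 0.30 | 28% / 12% | 0.86 | 0.07 |

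The remaining probability in each row is a tie. With equal true risk, counting every SAE makes each arm equally likely to show the higher count, whatever a1 and a2 are.

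**Step 4. What the planned test would do.** Fisher's exact test with 20 per arm gives p = 0.66 for 4 vs 2, 0.18 for 5 vs 1, 0.09 for 6 vs 1 and 0.047 for 5 vs 0. Attribution would seldom produce a significant result. Its effect is on the observed proportions, which is how a pilot of this size will mostly be read.

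**The case against.** A reader might infer that attribution, and not event frequency, decides which arm looks safer. The documents do not support that. The primary safety endpoints need no relatedness judgement, nor do three of the four secondary safety endpoints, mortality or cardiovascular admissions. A creatinine rise that meets the injury definition, a heart failure admission or a fall in LVEF is counted elsewhere whatever its cause is said to be.

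Three further objections have weight:

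- The row also counts SAEs related to the procedure. Both arms undergo the same kind of invasive left ventricular procedure, so this limb applies to both and narrows any difference in attribution.
- Related SAEs are not limited to expected ones. It would be wrong to say that the metric cannot show an unforeseen device risk. It misses such a risk only when nobody recognises the event as related.
- A related-SAE proportion is a legitimate device-safety measure, and the rates and attribution splits above are assumed.

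A reader might also infer that relatedness is judged unmasked. The article does not say who judges it. Masked adjudication may stand in the full protocol, and its absence from a condensed article is no finding. Masking would reduce the difference in attribution, but a related-only count would still not be a measure of SAE frequency. The mismatch between the row and its rationale therefore stands, as does the residual gap in Step 2.

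**Conclusion.** The point holds for one secondary endpoint. The definition does not match its stated purpose, it leaves some SAEs uncounted in any endpoint, and a comparison between arms on it can reflect attribution as well as frequency. The mismatch and the gap can be read directly from Table 3 and rest on no assumption.

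The size of the attribution effect is illustrative. With 70% against 30% attribution and a true risk of 20% to 40%, the arm with more attribution shows the higher count with probability 0.72 to 0.86. With 60% against 40% at a true risk of 30%, it is 0.62. The direction of any tilt is unknown. Overall safety does not rest on this metric, and no other figure in the plan changes. The correction is worth making because it is cheap, but it does not put the trial's safety assessment in doubt.

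**What to change.** In Table 3, make the SAE-frequency summary the proportion of patients in each arm with at least one SAE of any cause, from the procedure to the end of follow-up. Keep the present row beside it and change its rationale so that it is labelled as related SAEs only. Make the change before outcomes are compared by arm.

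The cost is one row and a change of wording. Table 2 already schedules adverse event review at the procedure, at discharge and at all three study visits, and an event has to be recorded before its relatedness can be judged, so no new visit is needed. The downside is that background disease events dilute the any-cause contrast; showing both lines offsets this. The any-cause count removes the dependence on relatedness, though not on the judgement of whether an event is serious.

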### Eligibility

Inclusion and exclusion criteria are presented in Table 1. Briefly, eligible patients must have a documented history of sustained monomorphic VT in the setting of ICM with a left ventricular ejection fraction (LVEF) of ≥20%. Important exclusion criteria include the presence of mechanical valves or a left ventricular (LV) assist device; patients with suspected epicardial substrate will also be excluded. Potential participants will be identified and approached in outpatient electrophysiology clinics or in the inpatient setting. After reviewing a study information sheet, discussing the study with the research coordinator, and having all their questions addressed, interested subjects will provide a written informed consent before enrolling in the study.

**Table 1 tbl1:** Study inclusion and exclusion criteria

Inclusion criteria		Exclusion criteria
Age ≥18 y		Unable to provide an informed consent
Ischemic heart disease with previous myocardial infarction		Idiopathic VT
LVEF ≥20% estimated by TTE within 90 d before enrollment		Mobile LV thrombus
Documented sustained monomorphic VT with any of the following characteristics:		Acute coronary syndrome within the preceding 2 mo (if incessant VT ≥1 mo before enrollment)
	≥2 documented episodes in patients with ICD	Comorbidity likely to limit survival to <12 mo
	≥1 documented episode in patients without ICD	New York Heart Association class IV heart failure
	Recurrent VT despite antiarrhythmic medications (ineffective, contraindicated, or not tolerated) or ICD interventions	Estimated glomerular filtration rate <30 mL/min/1.73 m^2^
Provision of a signed and dated informed consent form		Thrombocytopenia or coagulopathy
Stated willingness to comply with all study procedures and availability for the duration of the study		Contraindication to heparin
		Pregnancy or lactation
		Cardiac surgery within the past 2 mo
		Active infection
		Clinical, laboratory, or imaging evidence of active ischemia
		Severe left heart valvular heart disease (aortic/mitral stenosis or regurgitation)
		Any concomitant congenital heart disease
		Previous catheter or surgical ablation of VT within the past 2 mo
		Anticipated need for epicardial mapping and ablation
		For individuals with no preexisting ICD: ineligibility for an ICD implant
		Preexisting LVAD or other hemodynamic assist device
		Present mechanical heart valve
		Cardiogenic shock unless it is caused by incessant VT

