### Follow-up

The outline of the follow-up data collection strategy is presented in Table 2. Primary and procedural efficacy along with adverse event review will be performed immediately after the procedure and at the time of hospital discharge. Study visits 1 (7-40 days after the procedure) and 2 (90 ± 30 days after the procedure) will include functional assessment, ICD interrogation, and adverse event review. The final study visit (day 180 ± 30 after the procedure) will be a comprehensive assessment that will include transthoracic echocardiography and the 36-item short form health survey.

**Table 2 tbl2:** Schedule of activities

Procedures	Screening and enrollment/baseline, day −90 to −1	Ablation procedure	Discharge	Study visit 1, day 7–40∗	Study visit 2, day 90 ± 30∗	Final study visit, day 180 ± 30
Informed consent	X					
Demographics	X					
Medical history	X					
Physical examination	X		X			X
NYHA assessment	X			X	X	X
Vital signs	X		X			X
TTE†	X					X
ECG	X					X
ICD interrogation‡	X	X		X	X	X
SF-36	X					X
Adverse event review and evaluation		X	X	X	X	X
Complete case report forms	X	X	X	X	X	X

ECG = electrocardiogram; ICD = implantable cardioverter-defibrillator; NYHA = New York Heart Association; SF-36 = 36-item short form health survey; TTE = transthoracic echocardiogram.

∗ In-office visit or telephone/virtual visit. ICD interrogation can be monitored remotely.

† TTE at baseline to be performed within 6 months of enrollment.

‡ ICD interrogation can be performed via remote monitoring.

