### Statistical analysis and power calculations

The primary null hypothesis is that the total ablation time needed for complete LAVA elimination (ie, primary efficacy metric) will not be different between the 2 study arms. This hypothesis will be tested using a 2-sample *t* test.

PFA lesion delivery time will be, by design, shorter (3 2.5-second pulse trains = 7.5 seconds per ablation site) than RFA (at least 30 seconds per lesion). Furthermore, effective RFA lesion dimensions may vary widely depending on the distribution of myocardial scar, whereas PFA lesions are expected to be more consistent.^25^^,^^38^ Therefore, we envisage the time needed to eliminate targeted LAVAs to differ by at least 50% between the 2 study arms. With a desired power of 80% and a significance level of 0.05, the predicted minimum enrollment is 36 patients (18 in each study arm). This will be increased to 40 patients to allow for a 10% withdrawal rate. 10 additional patients will be screened to allow for possible screen failures.

The secondary efficacy and both primary and secondary safety endpoints will be analyzed using *t* test, rank sum test, or Fisher’s exact test, as appropriate. Time-dependent outcomes will be analyzed as landmark events. However, if the event rates and/or dropout rates are high in either group (≥20%), time-to-event methodology will be adopted (Cox regression and Fine-Gray competing risk models, as appropriate). Univariate and multivariable models will be used.

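### Only unadjusted tests are named for day-180 LVEF change, although baseline LVEF is collected in every patient; adjusting for it would give a modest gain in precision at no data cost

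*Protocol article*

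**What the plan says.** Table 3 (Endpoints) places "Changes in LVEF and/or new wall motion abnormalities at follow-up TTE (180 d") among the secondary safety endpoints of particular relevance to PFA. The Discussion explains that large, uniform PFA lesions might affect contractility and says the trial "will pay particular attention to any perturbations in LVEF and/or evidence of new wall motion abnormalities after ablation".

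Statistical analysis and power calculations states: "The secondary efficacy and both primary and secondary safety endpoints will be analyzed using *t* test, rank sum test, or Fisher’s exact test, as appropriate". After a sentence that brings in Cox and Fine-Gray models if event or dropout rates are high, the paragraph ends: "Univariate and multivariable models will be used". That sentence names no endpoint and no covariate.

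Both LVEF measurements are already planned. Table 1 (Eligibility) requires "LVEF ≥20% estimated by TTE within 90 d before enrollment". For follow-up: "The final study visit (day 180 ± 30 after the procedure) will be a comprehensive assessment that will include transthoracic echocardiography". Trial design describes 1:1 allocation in blocks of 4 and mentions no stratification by LVEF.

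**The concern.** Where a continuous outcome is measured before and after treatment, the baseline value usually explains part of the follow-up value. A t test or rank sum test on the change uses baseline only by subtracting it, which fixes the slope at 1. If the true slope is below 1, two things follow. The contrast between arms has more variance than it needs. And when the arms differ at baseline by chance, the arm that starts higher tends to fall more through regression to the mean, so the contrast is pushed in the direction opposite to the imbalance.

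This matters somewhat more here than for an ordinary secondary endpoint. The question is one of harm, so imprecision makes a real loss of contractility easier to miss. With about 20 patients per arm, a chance baseline difference of noticeable size is also quite possible.

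**Working it through.** **Inputs from the article.** 40 patients randomised 1:1, so 20 per arm. The sample-size paragraph asks for 18 per arm (36 in total) and allows 10% withdrawal: 36/0.9 = 40, which reproduces. That calculation concerns ablation time. The article gives no power figure for LVEF, so there is none to reproduce.

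**Assumed inputs.** The article gives neither the correlation rho between baseline and day-180 LVEF nor an LVEF standard deviation σ. I take rho from 0.3 to 0.9, σ equal at both times and, where LVEF points are needed, σ = 10. Tests are two-sided at 0.05. The 80% starting power is a reference value, not a claim about the trial's power for LVEF.

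**Variance.** Per patient, the quantity behind the contrast between arms has variance

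- change score: 2(1 − rho)σ²
- ANCOVA: (1 − rho²)σ²
- raw day-180 value: σ²

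The ratio of ANCOVA to change score is (1 − rho²)/[2(1 − rho)] = (1 + rho)/2. Estimating the slope costs a factor of about 1 + 1/(N − 4), which is 1.028 at N = 40 and 1.031 at N = 36.

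**Power.** For a change-score t test with 20 per arm (38 df), 80% power needs a noncentrality of 2.875. For ANCOVA, divide this by the square root of the corrected ratio and use 37 df. At rho 0.5 the corrected ratio is 0.75 × 1.028 = 0.771, the noncentrality is 2.875/√0.771 = 3.27, and power is 89%.

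| rho (assumed) | (1+rho)/2 | corrected, N = 40 | ANCOVA power, 20 per arm | ANCOVA power, 18 per arm |
|---|---|---|---|---|
| 0.3 | 0.65 | 0.668 | 92.9% | 92.8% |
| 0.5 | 0.75 | 0.771 | 89.0% | 88.9% |
| 0.7 | 0.85 | 0.874 | 85.0% | 84.8% |
| 0.8 | 0.90 | 0.925 | 82.9% | 82.8% |
| 0.9 | 0.95 | 0.976 | 80.9% | 80.7% |

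From a starting power of 60% with 20 per arm, rho 0.5 gives 71%. A simulation with 18 per arm and 4,000 runs gave variance ratios of 0.76, 0.86 and 0.92 at rho 0.5, 0.7 and 0.8. The corrected formula at N = 36 gives 0.77, 0.88 and 0.93.

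**In LVEF points** (σ = 10, 18 per arm, normal approximation). The detectable difference at 80% power is SD × √(2/18) × (1.960 + 0.842). Moving from change score to ANCOVA, it falls from 9.3 to 8.2 points at rho 0.5, from 7.2 to 6.8 at 0.7, and from 5.9 to 5.7 at 0.8.

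**Where the gain ends.** With N = 36 the corrected ratio reaches 1 when (1 + rho)/2 × 1.031 = 1, that is at rho of about 0.94. Above that ANCOVA loses slightly, by at most about 3% of variance.

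**Chance imbalance.** The SD of the baseline difference between arms is √(2/20) = 0.32 patient SDs with 20 per arm. With 18 per arm and σ = 10 it is 10 × √(2/18) = 3.3 points, so a 5-point difference is 1.5 standard errors. Given such a difference, the change-score contrast shifts by −(1 − rho) × 5 and a raw day-180 comparison by rho × 5:

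| rho (assumed) | change score | raw day-180 value |
|---|---|---|
| 0.5 | −2.5 | +2.5 |
| 0.7 | −1.5 | +3.5 |
| 0.8 | −1.0 | +4.0 |

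The change score thus removes the imbalance and goes past it. Above rho 0.5 its remaining shift is smaller than that of the raw comparison.

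**The case against.** **The target analysis is inferred.** The article offers a menu of tests to be used as appropriate and assigns none to LVEF. The and/or wording could also be read as one yes/no safety event for Fisher's exact test, in which case the variance comparison does not apply. This stands, and it is why the point is conditional on LVEF change being compared as a continuous outcome. It also shows that the endpoint needs splitting, because no single test on the menu handles a continuous change joined to a binary finding.

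**The multivariable sentence might cover it.** The text does not exclude that. But the sentence directly follows the time-to-event models and names neither LVEF nor a covariate, so it cannot be relied on to provide a baseline-adjusted comparison.

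**Such detail belongs in the SAP.** A missing covariate list would be no finding in a condensed article. Here, however, the article does name the tests for these endpoints, and all of them are unadjusted.

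**Stronger readings to resist.** A reader might infer that chance imbalance is left uncorrected. It is not: the endpoint is a change, so baseline is subtracted, and the fault is over-correction. A reader might infer that the change score is the least precise standard analysis. Against the raw day-180 comparison that is true only for rho below 0.5, since 2(1 − rho) is less than 1 above it. A reader might infer that the planned test is invalid. Under randomisation it is unbiased on average, and its standard error already reflects chance imbalance; the shifts shown in the working are conditional on an observed imbalance.

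**The weight is small.** This stands. It is one secondary safety endpoint in a 40-patient pilot, the Limitations text already stresses small size, and the article ties no decision rule to LVEF.

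**Conclusion.** The point holds as a minor, cost-free improvement. The tests named for the secondary safety endpoints are unadjusted, baseline LVEF is available in every patient, and a baseline-adjusted comparison is more precise than a change score for any correlation up to about 0.94 at this sample size. After the small-sample correction (N = 36), the saving in variance is about 23% at rho 0.5, 12% at 0.7, 7% at 0.8 and 2% at 0.9. From a reference power of 80%, that is a gain of about 9, 5, 3 and 1 percentage points.

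These sizes rest on an assumed rho, on equal variances at the two times, and on LVEF change being analysed as continuous. The figures in LVEF points also rest on the assumed SD of 10. The documents do not support a claim that the planned comparison is biased or invalid. What they support is that a more efficient analysis of an endpoint the authors themselves emphasise is available from data already collected, and that the article does not clearly provide for it.

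**What to change.** In Statistical analysis and power calculations, state that day-180 LVEF will be compared between arms by ANCOVA with baseline LVEF as covariate, reporting the adjusted difference with its 95% CI. Split the and/or endpoint and analyse new wall motion abnormality as a separate yes/no outcome with Fisher's exact test. Say which endpoints the multivariable-models sentence applies to.

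Baseline LVEF would become the covariate, so its window should be stated once. Table 1 gives "LVEF ≥20% estimated by TTE within 90 d before enrollment", while the footnote to Table 2 has "TTE at baseline to be performed within 6 months of enrollment". The two must be reconciled.

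The cost is one or two sentences and one degree of freedom. No new data, visits or patients are needed.
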